## **Methodological Procedures**

### **Participants**

Twelve apparently healthy adults aged between 21 to 34 years will be included in this study. These will be recruited from the professional network of GCP. We do not expect these adults to be enrolled in any other scientific study besides PUMPING ARTERIES. Informed written consent will be signed by volunteers prior to the first evaluation day (Figure 1) in accordance with approval by the Ethical Committee of Faculdade de Motricidade Humana – Universidade de Lisboa. We expect recruited participants to be outwardly active with some experience in both aerobic and resistance exercise (~3–4 times/week, >3 months). No trained athletes will be included in the cohort. All participants will be healthy or perceived to be healthy based on the sport's medical examination or the preparticipation screening process. Exclusion criteria include any form of cardiovascular disease, more than one cardiovascular disease risk factor, resting hypertension (systolic blood pressure >140 mmHg, diastolic blood pressure > 90 mmHg), any prescription medication use, and currently smoking.

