### **Design**

The study is constructed as a randomized, cross-over, repeated-measures intervention. Participants will attend 4, separate, intervention sessions consisting of one group class of Bike, Pump Power, Global Training or no exercise (CON). There will be a minimum of 72 h between sessions [18, 37], and each session will consist of initial rest, experimental intervention, and recovery (Figure 1). Participants will be advised not to engage in any strenuous physical activity at least 48 hours before the study days. Body composition and cardiorespiratory fitness for each participant will be evaluated prior to- and following to- the CON session, respectively.

|                           | WEEK 1 |   |   |   |   |   |   | WEEK 2 |   |   |   |   |   |   | WEEK 3 |   |    |    |    |    |    |
|---------------------------|--------|---|---|---|---|---|---|--------|---|---|---|---|---|---|--------|---|----|----|----|----|----|
|                           | 1      | 2 | 3 | 4 | 5 | 6 | 7 | 1      | 2 | 3 | 4 | 5 | 6 | 7 | 8      | 9 | 10 | 11 | 12 | 13 | 14 |
| ENROLLMENT         |        |   |   |   |   |   |   |        |   |   |   |   |   |   |        |   |    |    |    |    |    |
| Eligibility Screen        |        |   |   |   |   |   |   |        |   |   |   |   |   |   |        |   |    |    |    |    |    |
| Randomization             |        |   |   |   |   |   |   |        |   |   |   |   |   |   |        |   |    |    |    |    |    |
| Informed Consent          |        |   |   |   |   |   |   |        |   |   |   |   |   |   |        |   |    |    |    |    |    |
| INTERVENTIONS*     |        |   |   |   |   |   |   |        |   |   |   |   |   |   |        |   |    |    |    |    |    |
| Bike                      |        |   |   |   |   |   |   |        |   |   |   |   |   |   |        |   |    |    |    |    |    |
| Pump Power                |        |   |   |   |   |   |   |        |   |   |   |   |   |   |        |   |    |    |    |    |    |
| Global Training           |        |   |   |   |   |   |   |        |   |   |   |   |   |   |        |   |    |    |    |    |    |
| Control                   |        |   |   |   |   |   |   |        |   |   |   |   |   |   |        |   |    |    |    |    |    |
| ASSESSMENTS        |        |   |   |   |   |   |   |        |   |   |   |   |   |   |        |   |    |    |    |    |    |

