**FIGURE 1: TIMELINE AND MAIN OUTCOME VARIABLES OF PUMPING ARTERIES**

\* INTERVENTIONS WILL BE RANDOMIZED. THE TIMELINE HEREIN DISPLAYED IS MERELY A GRAPHIC REPRESENTATION OF A PARTICIPANT'S ACTIVITIES FOLLOWING RANDOMIZATION.

In each session, participants will initially undertake 20-min of supine rest on a cushioned examination table with resting energy expenditure measured by indirect calorimetry (K5, Cosmed, Rome, Italy) and heart rate and blood pressure recorded continuously using digital plethysmography technique (Finapres® Nova, Ohmeda, 2 Louisville, Colorado, USA), followed by regional assessments of PWV and pulse wave analysis of the aortic, brachial and femoral arteries on the right side of the body using applanation tonometry (Colson Analyze, ALAM Medical, Paris, France), and carotid arterial stiffness indices and wave intensity analysis using an ultrasound (Arietta V60, Hitachi Aloka Medical Ltd, Mitaka-shi, Tokyo, Japan). In the time following, participants will perform one of three exercise sessions (Bike, Pump Power or Global Training). Exercise sessions will consist of either a 45-minute class of Bike, Pump Power, and Global Training, while energy expenditure will be continuously measured by indirect calorimetry (K5, Cosmed, Rome, Italy) (Figure 2). These sessions are characterized by distinct metabolic demands, representing the typical sessions provided by gyms and health clubs to improve or maintain cardiovascular health. In the control condition, the participants will remain quietly seated for 45-min, maintaining a good posture. Only one participant will be tested per class with approximately 10-20 non-research participants also performing each group fitness class alongside the research participants. Upon completion of each intervention/session, participants will return immediately to the examination table and recover in the supine position for 30-min while hemodynamic and stiffness indices are reevaluated at 10, 20- and 30-min following recovery and compared to those at rest.

|                       | Rest |    | Exercise Session | Recovery |    |    |
|-----------------------|------|----|------------------|----------|----|----|
|                       | 15   | 20 | 45               | 10       | 20 | 30 |
| Advanced Hemodynamics |      |    |                  |          |    |    |
| Arterial Stiffness    |      |    |                  |          |    |    |

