**FIGURE 2: EXPERIMENTAL DESIGN OF PUMPING ARTERIES**

Participants will be blinded to the order of the experimental interventions until arrival at the laboratory. All sessions will be conducted in the morning with each participant performing sessions at the same time of the day to minimize any potential diurnal variation. Participants will be instructed not to ingest any food or drink (except water) 4h before the sessions, and to avoid alcohol, caffeine, and vigorous exercise for at least 12h preceding each session [38].

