### **Statistical Analysis and Data Monitorization**

Based upon a medium effect size of 0.154 derived from published changes in aortic PWV within-between modes of exercise [18], an a priori power analysis suggested that 22 participants are required to detect significant differences within-between groups, conditions and time points ( $1-\beta = 80\%$ ,  $\alpha = 0.05$ ). All data will be collated and/or analyzed using Microsoft Excel (v15.29.1, Microsoft Corporation, Redmond, Washington, United States) and Statistical Package for the Social Sciences version 24 (IBM, Armonk, New York, United States) software with results presented as mean  $\pm$  SD. Due to technical issues, missing data (~4–5%) may be evident during the study and subsequently should be replaced by averaging values before and after the missing value for the relevant variable prior to analysis.

Comparisons between interventions (Bike, Pump Power, Global Training and Control) over time (Rest vs. post-intervention time points) for indices of autonomic and vascular function will be examined via two-way

(intervention × time), repeated measures analysis of variance (ANOVA) and adjusted for sex and activity energy expenditure. Session differences for indices of autonomic and vascular function and energy expenditure will be analyzed using a one-way repeated measures ANOVA. Post-hoc comparisons will be conducted via Bonferroni's tests. Statistical significance will be set at  $p < 0.05$ .

The database will be stored in the GCP private server throughout the study period. The GCP lab will be responsible for management, storage and is the single user of the complete database.

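### Treating Rest as a level of time, with no period term, leaves the class comparison unbiased but less precise than adjusting the recovery values for session Rest

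*Protocol*

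**What the plan says.** Protocol, Design: "The study is constructed as a randomized, cross-over, repeated-measures intervention". Each participant attends three class sessions and one control session. The note to Figure 1 adds "INTERVENTIONS WILL BE RANDOMIZED". No set of sequences or balancing rule is described.

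The text under Figure 1 has each session begin with a supine rest measurement. The haemodynamic and stiffness indices are repeated 10, 20 and 30 minutes into recovery and compared with rest.

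Protocol, Statistical Analysis and Data Monitorization: "Comparisons between interventions (Bike, Pump Power, Global Training and Control) over time (Rest vs. post-intervention time points) for indices of autonomic and vascular function" are to be examined by an intervention × time repeated-measures ANOVA. The adjustments are sex and activity energy expenditure. Neither a period term nor a session-Rest covariate is named.

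On sample size, Participants says "Twelve apparently healthy adults aged between 21 to 34 years will be included in this study", whereas the statistical section says "an a priori power analysis suggested that 22 participants are required".

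**The concern.** With Rest as one of four times and four conditions, the class effect is carried by the interaction, which has (4−1)×(4−1) = 9 degrees of freedom. Its contrasts against Rest are differences in change from Rest. In a crossover each participant is already their own control, so full subtraction of the session's Rest value is not needed for a fair comparison. Regression on that value removes the same nuisance variation without carrying all of Rest's own error into the result.

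The intervention main effect of the planned ANOVA does not solve this. It averages Rest with the three recovery times, so a sustained post-exercise effect is diluted to 3/4.

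Precision is at stake. The Protocol intends to include 12 participants while its own power statement asks for 22, so any gain that needs no extra visit is worth having. The model, the role of Rest and the covariates are all stated in the Protocol, so this concerns a choice already made and not a detail left to a SAP.

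**Working it through.** **The plan's own figure.** The 22 rests on a "medium effect size of 0.154 derived from published changes in aortic PWV within-between modes of exercise", with 80% power and α = 0.05. It cannot be reproduced, because the metric of 0.154, the numbers of groups and measures, and the correlation are not given. With correlation 0.5, four groups and four times, the standard repeated-measures formula gives 86 (0.154 read as f), 16 (as f²) or 14 (as η²). Other settings give exactly 22, so the figure cannot be called wrong. It matters here only for the layout of sequences.

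**Inputs.** From the Protocol: four conditions, Rest plus three recovery times, 12 participants. Assumed: r, the Rest-recovery correlation within a session after participant effects are removed, ranged from 0.2 to 0.9. Variances are in units of the within-participant variance.

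**One recovery point.** Change from Rest has variance 2(1−r). The Rest-adjusted value has variance 1−r². The ratio is (1−r²)/[2(1−r)] = (1+r)/2.

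| r | change | adjusted | ratio | 12 act like |
|---|---|---|---|---|
| 0.2 | 1.60 | 0.96 | 0.60 | 20 |
| 0.5 | 1.00 | 0.75 | 0.75 | 16 |
| 0.8 | 0.40 | 0.36 | 0.90 | 13.3 |
| 0.9 | 0.20 | 0.19 | 0.95 | 12.6 |

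**Mean of the three recovery points, equal correlations.** Change: (1+2r)/3 + 1 − 2r = 4(1−r)/3. Adjusted: (1+2r)/3 − r² = (1−r)(1+3r)/3. The ratio is (1+3r)/4, which is 0.40, 0.625, 0.85 and 0.925 at the same four values of r.

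**Cost of estimating the slope.** Simulated at n = 12 with the slope estimated, the ratios were about 0.62, 0.78, 0.95 and 0.99 for one point, and 0.42, 0.66, 0.91 and 0.97 for the mean of three.

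**Power.** Take the same sustained effect in all three classes against control, n = 12, sized so that the 9-df interaction has 80% power. A 3-df test of mean change has 92%. The Rest-adjusted 3-df test with period, on balanced sequences, has 99% (r = 0.5), 95% (r = 0.8) or 93.5% (r = 0.9). These figures treat the slope as known, so they are slightly optimistic. Much of the step from 80% to 92% comes from concentrating the test on 3 df, not from the covariate.

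**Period.** Per session-level contrast at n = 12, period takes the error df from 33 to 30, and session Rest takes it to 29. The two-sided 5% t value moves from 2.035 to 2.042 and 2.045. Participant mean Rest is a between-participant term and costs nothing here. With period fitted, four sequences of three participants have efficiency 1.00. Unrestricted random orders average 0.91 (5th percentile 0.82).

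Simulated results for a trend of 0.5 within-participant SD per visit that reaches the analysed quantity:
- Balanced orders without period: estimated variance 0.245 against a true 0.169, and type I error 0.019.
- Random orders: true variance 0.225 without period and 0.187 with it.
- Random orders with no trend: fitting period raises true variance from 0.167 to 0.184, a ratio of 1.10.

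Fitting period therefore pays reliably only when orders are balanced.

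**The case against.** The strongest defence is that the planned test is valid and matches the aim. The Purpose is to compare the time-course of recovery, and the recovery values are to be set against rest. The interaction tests that directly and without bias. This stands, and it is why the Rest-versus-recovery comparison within each class should be kept. The size of the gain also rests on an r that the documents do not supply.

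Several stronger readings are tempting but not supported:

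- *The order is unbalanced.* The Protocol says the order is randomised and that "Participants will be blinded to the order of the experimental interventions until arrival at the laboratory". It does not say how sequences are generated. Any figure for chance imbalance would assume simple randomisation, which is nowhere stated.
- *Visit effects contaminate the class comparison.* A shift common to a whole session enters Rest and all recovery values equally and cancels from the interaction. Only a visit effect on the rest-to-recovery change would remain, and nothing in the text points to one. The cancellation is incomplete once Rest becomes a covariate with a slope below 1, which is why period belongs in the revised model.
- *Subtracting Rest always adds noise.* Against recovery values alone (variance 1), change has variance 2(1−r). This is larger only if r is below 0.5; at r = 0.8 it is 0.40.
- *A mixed model removes the sphericity assumption.* Random participant and session intercepts still imply equal correlations among the three recovery times. In a simulation with AR(1) correlation 0.8 and n = 12, type I error was 6.4% for that structure and 6.4% for uncorrected repeated-measures ANOVA on the same three points.
- *The gain is free.* It costs about four residual degrees of freedom, and period on unbalanced orders can lose precision.

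**Conclusion.** The point holds as one of efficiency. Rest as a level of time gives an unbiased interaction test, but one less precise than an analysis of the recovery values adjusted for session Rest. At r = 0.2 to 0.9 the single-point variance ratio is 0.60 to 0.95 in theory and about 0.62 to 0.99 at n = 12. So 12 participants would act like between about 19 (12/0.62) and 12 (12/0.99). The gain is substantial for low or moderate r and negligible for high r.

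This assumes equal variances at Rest and recovery and a linear relation between them. The mean-of-three figures also assume equal correlations. The missing period term is not a bias in the planned interaction; it matters mainly once the model is changed. The case for acting is that the Rest values are collected anyway and the number to be included is small.

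**What to change.** Make the between-class comparison with a linear mixed model of the 10, 20 and 30 min values. Include intervention, time, intervention × time, period, session Rest and participant mean Rest; the last separates the within- from the between-participant slope. Use a within-session covariance that does not assume equal correlations, or apply a small-sample correction. Keep the Rest-versus-recovery comparison within each class as a descriptive or secondary analysis.

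State the sequence scheme: allocate participants as evenly as possible to the four sequences of a 4 × 4 Williams square, in which each condition occurs once per period and follows every other condition equally often. With N = 12 that is three per sequence. N = 22 is not divisible by four, but a near-even layout still has efficiency 0.997. The 12 in Participants and the 22 in the statistical section must be reconciled first.

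The cost is a randomisation list, revised model wording and about four residual degrees of freedom (three for period, one for session Rest). No visit or measurement is added. If r proves high, little will have been gained.

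### The planned repeated-measures ANOVAs need complete cases, so one missed session would cost a participant's other attended sessions; a correctly specified mixed model would keep them

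*Protocol*

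**What the plan says.** The Design section requires each person to supply four sessions: "Participants will attend 4, separate, intervention sessions", covering three classes and a no-exercise control. Within each session there is a rest measurement, and "stiffness indices are reevaluated at 10, 20- and 30-min following recovery and compared to those at rest". That is 4 × 4 = 16 values per person for each variable.

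The section Statistical Analysis and Data Monitorization fixes the method. The intervention-by-time comparison is a two-way "repeated measures analysis of variance (ANOVA) and adjusted for sex and activity energy expenditure". Session differences "will be analyzed using a one-way repeated measures ANOVA". The software is "Statistical Package for the Social Sciences version 24".

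The same section anticipates gaps of one kind: "Due to technical issues, missing data (~4–5%) may be evident during the study". These are to be replaced by the mean of the values before and after the gap. The protocol has no provision for a missed session, no attrition allowance and no replacement of participants. The Participants section plans 12 people.

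**The concern.** A classical repeated-measures ANOVA with all four interventions as within-subject levels works on complete sets. The usual SPSS repeated-measures procedure drops a person with any empty cell. Someone who attends three sessions and misses one then contributes nothing, although 12 of their 16 values were recorded.

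The averaging rule does not rescue such a person. It can fill a gap at 10 or 20 minutes, where there is a reading on each side. It cannot fill a rest value (nothing before it in the session), a 30-minute value (nothing after it) or a whole session.

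With 12 participants each person is 1/12, about 8%, of the sample. What is at stake is precision, plus a comparison that may rest only on people who attended everything.

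**Working it through.** **The plan's own figure.** The protocol states 22 participants for 80% power at α = 0.05 and an effect size of 0.154. Neither the type of effect size nor the correlation between repeated values is given. Assume Cohen's f, the 4 × 4 within-subject interaction, correlation ρ = 0.5 and sphericity:

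- λ = f² × N × 16/(1 − ρ) = 0.154² × 22 × 16/0.5 = 16.7
- df = 9 and 9 × (22 − 1) = 189
- power = 0.81, so N = 22 is reproduced. At ρ = 0.7 the answer is N = 14, so the match depends on the assumption.

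With f = 0.154 and ρ = 0.5, power is 0.48 for 12 complete participants, 0.43 for 11, 0.39 for 10 and 0.30 for 8. The conflict between 12 and 22 is a separate matter; here it only makes each lost person more costly.

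**One missed session.** A full data set has 12 × 16 = 192 values per variable. One missed session leaves 192 − 4 = 188 recorded values. A complete-case ANOVA uses 11 × 16 = 176 and discards 12. A trial run on simulated data behaved this way: a repeated-measures ANOVA routine rejected the incomplete set and ran only after that person was removed, while a mixed model used all 188.

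**Expected loss.** The protocol gives no session-loss rate, so q is an assumption. If sessions are missed independently with probability q, the expected number of completers is 12 × (1 − q)⁴. The variance of a pairwise contrast from n completers is proportional to 2/n. It was compared with the variance using all attended sessions, over 4,000 simulated patterns per setting.

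| q | Completers of 12 | Contrast variance, complete cases vs all attended sessions |
|---|---|---|
| 3% | 12 × 0.97⁴ = 10.6 | about 9% larger |
| 5% | 12 × 0.95⁴ = 9.8 | about 16% larger |
| 10% | 12 × 0.90⁴ = 7.9 | about 36–38% larger |
| 0% | 12 | no difference |

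If people instead leave for good, with a 3% to 10% risk before each of visits 2 to 4, the increase is about 4% to 13%.

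**Analytic check.** A person with 3 of 4 sessions carries 2/3 of a completer's information on the contrasts. If 3 of 12 each miss one session and the classes missed differ, the information is 9 + 3 × 2/3 = 11 completers against 9, and 11/9 = 1.22. If all three miss the same class, contrasts among the other three classes have variance 2/9 against 2/12, which is 33% larger. For contrasts involving the missed class it is 2/9 = 0.222 against (4/3)/9 + (2/3)/12 = 0.204, which is 9% larger.

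**Which mixed model.** The two-way ANOVA tests intervention against the intervention-by-participant error. A model with only a random participant effect pools all errors and ignores the deviation shared by the four readings of one session. This was simulated with complete data, 12 participants and no true effect:

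| Session variance ÷ residual variance (assumed) | Type I error, intervention | Type I error, interaction |
|---|---|---|
| 0.25 | about 19–20% | about 1.7% |
| 0.5 | about 29–31% | about 0.6% |
| 1 | about 42% | about 0.1% |

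The planned ANOVA holds about 5% for intervention in the same settings. The simpler model agrees with it only when the session variance is zero.

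**The case against.** **The protocol does not say that only completers are analysed.** This is correct. A reader might infer a stated completers-only policy, but the deletion is a consequence of the named method. The software is named and the procedure within it is not. The planned adjustment for activity energy expenditure, which is measured in each class and so varies by session, also fits poorly with the standard wide-format procedure. Even so, the method named is a repeated-measures ANOVA, and its classical form needs complete sets.

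**Missed sessions may be handled in a statistical analysis plan that is not shown.** This is fair for the detail of missing-data handling. It does not dispose of the point, because the protocol itself fixes the analysis method and an averaging rule that cannot work for these gaps.

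**The loss rate is assumed.** This stands. The only figure in the protocol is about 4–5% of values, attributed to technical causes. Participants are healthy, already active and seen over about three weeks, so attendance may be full and the loss zero.

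**A class stopped early yields no readings.** A reader might infer this from "Upon completion of each intervention/session, participants will return immediately to the examination table". The sentence describes the ordinary sequence, and nothing says that readings are withheld after an early stop. That reading is not relied on here.

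**A mixed model would cure selection.** It would not. If people avoid one demanding class, that class is still seen only in those who did it. The model then recovers precision mostly in the other contrasts, as the 33% and 9% figures show.

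**Conclusion.** The point holds in a limited form. The protocol fixes a method that needs complete cases, and its one missing-data rule cannot restore a missed session or a missing rest or 30-minute value. Sessions already measured could therefore be lost from a sample of 12. Under an assumed independent session loss of 3% to 10%, about 10.6 to 7.9 participants are kept and pairwise contrast variance is about 9% to 36–38% larger than necessary. With full attendance there is no loss, and the planned ANOVA is not made invalid by this point.

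The documents do not support saying that the trial will be biased, or that its authors chose a completers-only analysis. The change is worth making because it is cheap, but only with a correctly specified model. The wrong random-effects structure would do more harm than the missing sessions.

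**What to change.** In Statistical Analysis and Data Monitorization:

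- Replace the two-way ANOVA by a linear mixed model (SPSS MIXED) using every attended session. Fixed effects: intervention, time, intervention × time and the planned sex adjustment. Keep the activity energy expenditure adjustment unless it is changed separately.
- Include random effects for participant and for participant × intervention (the session), plus participant × time or an equivalent within-session covariance, with Satterthwaite degrees of freedom. State that a participant-only random effect is not to be used for this analysis.
- For the one-way comparison, with one value per session, use a mixed model with a random participant effect, which suffices there.
- Report the number of completed sessions per intervention.

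The cost is protocol wording, with the same software and data. The downsides are that a covariance structure must be chosen in advance, and that the model deals with selective non-completion only under missing at random, which should be stated as an assumption.

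### Adjusting the within-participant ANOVA for sex removes no bias, and if sex is entered as an uncentred covariate the intervention × time test no longer addresses the average effect

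*Protocol*

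**What the plan says.** Under Design, the protocol states: "The study is constructed as a randomized, cross-over, repeated-measures intervention". It adds that "Participants will attend 4, separate, intervention sessions", namely three fitness classes and a no-exercise control. Hemodynamic and stiffness indices are measured at rest and at 10, 20 and 30 minutes of recovery.

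Under Statistical Analysis and Data Monitorization, the interventions are compared over time by a two-way (intervention × time) "repeated measures analysis of variance (ANOVA) and adjusted for sex and activity energy expenditure". The software is "Statistical Package for the Social Sciences version 24". The section does not say whether sex is a covariate or a between-participant factor, how it is coded, or whether it is centred. No section gives the expected numbers of men and women.

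The same section gives the basis for sample size: "Based upon a medium effect size of 0.154 derived from published changes in aortic PWV within-between modes of exercise", from which "an a priori power analysis suggested that 22 participants are required" at 80% power and α = 0.05. Participants, however, states: "Twelve apparently healthy adults aged between 21 to 34 years will be included in this study". Both sample sizes are therefore carried through below.

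**The concern.** Each participant is their own control. A quantity that is constant within a participant drops out of every difference between sessions or time points, so sex cannot bias the intervention × time comparison in a complete cross-over. The adjustment has no confounding to remove.

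It may do harm, depending on how it is fitted. When a participant-level covariate is added to a repeated-measures general linear model, each within-participant contrast is regressed on that covariate. The F test for intervention × time then tests the intercepts of those regressions, which is the effect where the covariate equals zero. With sex coded 0/1, that is the effect in one sex only. With sex coded 1/2, it is an extrapolation to a value that no participant has. The stated purpose is to compare classes in the participants as a whole. Under such a fit, the main p value would depend on an arbitrary coding and answer a different question.

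The covariate route is a natural reading for two reasons. The model is called two-way, whereas a sex factor would make it a three-way mixed design. Sex also shares its phrase with activity energy expenditure, which is continuous. This is an inference from the wording, not something the protocol states.

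**Working it through.** **Inputs from the protocol.** α = 0.05; target power 80%; effect size 0.154; required N = 22; enrolled N = 12; 4 conditions; 4 time points.

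**Assumptions.** The effect size is read as Cohen's f, since its metric is not named. The correlation between repeated measures is ρ = 0.5, since none is given. Sphericity holds, the sexes are equal in number unless stated, and there is no true sex difference in response.

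**Step 1: reproduce the stated sample size.** For the interaction in a 4 × 4 within-participant design:

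- df1 = 3 × 3 = 9 and df2 = 9(N − 1)
- λ = N × 16 × f² / (1 − ρ)
- N = 21: λ = 21 × 16 × 0.023716 / 0.5 = 15.94, power 0.786
- N = 22: λ = 22 × 16 × 0.023716 / 0.5 = 16.70, power 0.810

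The smallest N reaching 80% is 22, which matches the protocol under these assumptions. At N = 12, λ = 12 × 16 × 0.023716 / 0.5 = 9.11 and power is 0.476 before any adjustment.

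**Step 2: variance of what is tested.** Let s² be the between-participant variance of one contrast, and take 6 participants of each sex.

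- No covariate: the overall mean, variance s²/12
- Sex coded 0/1: the mean of the sex coded 0, variance s²/6, so efficiency (1/12)/(1/6) = 0.50
- Sex coded 1/2: the value at 0 is 2m₁ − m₂, variance 4s²/6 + s²/6 = 5s²/6, so efficiency (1/12)/(5/6) = 0.10
- Sex centred, or a factor with equal numbers: variance s²/12, so efficiency 1.0

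The efficiencies are the same for 11 + 11.

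**Step 3: power.** Multiply λ by the efficiency and use df2 = 9(N − 2).

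| How sex enters (equal sexes) | N = 22 | N = 12 |
|---|---|---|
| Not in the model | 0.81 | 0.48 |
| Centred, or between-participant factor | 0.81 | 0.47 |
| Uncentred covariate, 0/1 | 0.45 | 0.23 |
| Uncentred covariate, 1/2 | 0.11 | 0.08 |

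A simulation of 20,000 trials per setting at N = 22, calibrated to 80% unadjusted power, agrees: 0.446 (0/1), 0.106 (1/2), 0.797 (factor) and 0.806 (centred).

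**Step 4: unequal sexes, about 2:1.** A between-participant factor tests the equally weighted mean of the two sexes, with efficiency (1/N) / [(1/a + 1/b)/4] for a and b participants.

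- N = 22 as 15 + 7: efficiency 0.868, power 0.74
- N = 12 as 8 + 4: efficiency 0.889, power 0.42

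A centred covariate keeps efficiency 1.0 in both cases.

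**Step 5: sensitivity to ρ.** Each cell gives power with sex not in the model, then uncentred 0/1, then uncentred 1/2, for equal sexes.

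| ρ | N = 22 | N = 12 |
|---|---|---|
| 0.3 | 0.63 / 0.32 / 0.09 | 0.34 / 0.17 / 0.07 |
| 0.5 | 0.81 / 0.45 / 0.11 | 0.48 / 0.23 / 0.08 |
| 0.7 | 0.97 / 0.72 / 0.16 | 0.74 / 0.39 / 0.10 |

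The levels move with ρ but the ordering does not.

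**Step 6: if the sexes respond differently.** A simulation at N = 22 assumed equal numbers, independent errors, exactly opposite responses in the two sexes (peak 1 error SD) and a zero average effect. The uncentred test rejected in 20% (0/1) or 34% (1/2) of trials, against 5% when sex was centred. This is an extreme case, and shows only that the uncentred test does not control error for the average effect.

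**The case against.** The strongest reply is that the protocol never calls sex a covariate. Sex has two levels, so a between-participant factor is an ordinary choice, and with balanced sexes it costs almost nothing. A single additive sex term in a random-intercept model is also harmless. In one simulated 12-participant data set, the interaction F was 0.7310 without sex and with sex coded either 0/1 or 1/2. The coding matters only if each contrast is regressed on sex, which in effect adds sex × intervention × time terms. Further, activity energy expenditure is measured in each session, so it does not fit a single participant-level covariate column, and the planned model is not certain to be the one examined here. Factor or covariate, coding and centring are details that an analysis plan may settle, and that plan is not shown. Finally, the protocol cites work on sex differences in heart rate variability during recovery, so an interest in sex is reasonable.

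All of this stands, and it makes the power loss conditional. A reader might infer that the plan does test the effect at sex = 0, or that adjusting for sex inevitably loses most of the power. The documents support neither. The first depends on an unstated fit. The second describes 1/2 coding (0.81 to 0.11); with balanced 0/1 coding a little under half is lost at N = 22 and about half at N = 12.

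The reply does not supply a reason for the adjustment. The protocol prescribes it for the main comparison, where it has no bias to remove.

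**Conclusion.** The point holds in conditional form. What is certain from the design is that adjusting for sex removes no confounding from the intervention × time comparison. What is conditional is the harm: only an uncentred covariate in a repeated-measures general linear model moves the test to sex = 0. Power would then be roughly halved with 0/1 coding and largely lost with 1/2 coding, at either sample size. These figures rest on f = 0.154, ρ = 0.5, sphericity and equal sexes; the last three are assumptions, as is reading 0.154 as f. With 12 enrolled against 22 required, power on these inputs is already about 0.48, so there is little to spare. The change is worth making because it is almost free and protects the main test under every reading of the sentence.

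**What to change.** In Statistical Analysis and Data Monitorization, drop sex from the adjustment of the intervention × time comparison. If the sponsor wishes to keep it, state that sex is centred at its sample mean or entered as a between-participant factor. In either case, state that the intervention × time test is of the effect averaged over participants; with a factor and unequal numbers, say that the two sexes are weighted equally. Report any sex × intervention × time term as exploratory.

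The cost is one sentence and no new data. Dropping sex costs nothing. Keeping it costs one participant-level degree of freedom (power 0.810 to 0.809 at N = 22, and 0.476 to 0.472 at N = 12, with equal sexes). A factor with a split of about 2:1 costs more: power about 0.74 at N = 22 and 0.42 at N = 12.
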